### Analysis plan

#### Aim 1

The primary outcomes are the proportion of patients who reach clinical goals based on national guidelines for (a) aspirin use, (b) HTN control, (c) blood cholesterol management, and (d) smoking cessation assistance at the end of the intervention (12 months) period and 6 months post-intervention. Each of the four hypotheses referring to the four primary outcomes will be tested separately with a two-sided test with *α* = 0.05, i.e., no adjustment for multiple testing will be applied. The analysis of effect of PF on the ABCS outcome measures in the context of a stepped-wedge design will be based on a generalized linear mixed model (GLMM). In particular, to assess the intervention effect, we will use a Poisson model with random site and provider within site effects. Each model will be as follows:1$$ \log \left({C}_{it}\right)=\mu +{\beta}_1t+{\beta}_2{I}_{it}^{PF}+{\beta}_3{I}_{it}^{PF}\left(t-{s}_i\right)+\gamma {Z}_i+{b}_i+ \log \left({E}_{it}\right), $$

where *C*
_*it*_ is the number of patients in site *i* who (a) had received aspirin, (b) had controlled blood pressure, (c) had controlled cholesterol, or (d) received smoking cessation counseling during period *t*, for *t* ∈ (0, 1, …, 11). Each period is 3 months, and *t* = 0 is the baseline quarter. *I*
_*it*_^PF^ is an indicator variable, and *I*
_*it*_^PF^ = 1 if site *i* has been assigned to the PF intervention at period *t*, *I*
_*it*_^PF^ = 0 otherwise. *s* is the time period when the PF intervention begins for site *i. Z* is a site-level indicator variable, *Z* = 1 if site *i* has three or more providers, *Z* = 0 otherwise. *E*
_*it*_ is the number of patients at site *i* who were eligible to be counted during period *t*. The eligible pool of patients *E*
_*it*_ will be different for each outcome and has been described in detail in Table 1. Log(*E*
_*it*_), considered the “offset” in the Poisson regression model, is a random effect for site *i* with mean 0 and variance *σ*
_*b*_^2^. The estimation via model (1) takes into account a general time trend and allows for the intervention effects to grow over time following implementation of the intervention.

Our primary outcome of interest for each of the four models is proportion of patients who meet clinical goals (described above) at 12 months. In each model, this effect (after taking into account general time trends) would be captured by *β*
_2_ + 3*β*

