_3_. For the four primary outcomes, we will conduct tests with these null and alternative hypotheses: *H*
_0_ : *β*
_2_ + 3*β*
_3_ = 0 vs. *H*
_*A*_ : *β*
_2_ + 3*β*
_3_ ≠ 0. The models will be fit using the LME4 package using R software.

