## Appendix

### Power/effect size analysis

With the pre-specified number of sites (250) and design (wedge design with four strata starting 3 months apart, we investigate the intervention effects under each of the primary hypotheses in Aim 1, that are detectable with at least 80 % power of a two-sided significance test with *α* = 0.05. Conversely, we assess the power to detect effects that are clinically meaningful and realistic.

For each of the four outcomes, we are interested in comparing the proportion of eligible patients in a physician’s panel who meet compliance (i.e., appropriate blood pressure level, appropriate cholesterol level, indication that aspirin was recommended, and indication of referral for smoking cessation) in the third quarter after PF intervention with the compliance proportion at baseline. In particular, we are interested in the difference *d*
_*π*_ = *π*
_3_ − *π*
_0_, where *π*
_0_ is the baseline compliance rate, and *π*
_3_ is the third period compliance rate. The proportions *π*
_0_ and *π*
_3_ will be estimated by *C*
_0_/*E*
_0_ and *C*
_3_/*E*
_3_, respectively, where *C* is the number of patients in compliance and *E* is the number of eligible patients. We will use the model to estimate the difference *d*
_*π*_. However, because of the specific Poisson distributions of the data and the model that we will be using, the treatment effect is more naturally expressed as a ratio rather than a difference: *r*
_*π*_ = *π*
_3_/*π*
_0_.

We conducted the simulations varying the ratio *r*
_*π*_, but for the clarity of interpretation, we also present the effect as a difference *d*
_*π*_. Our goal is to find the *r*
_*π*_ ’ s (and *d*
_*π*_ ’ s) that would allow 80 % power of a two-sided test for significance with *α* = 0.05. We simulate the outcomes based on different assumptions about baseline compliance rates, random effects (which are at the scale of log(*C*)), and patient eligibility numbers. For each set of assumptions, 2000 data sets were generated using the GLMM model given in Eq. (2).

2 $$ \log \left({C}_{jt}\Big|{d}_j\right)=\mu +{\beta}_1t+{\beta}_2{I}_{jt}^{\mathrm{PF}}+{\beta}_3{I}_{jt}^{\mathrm{PF}}\left(t-{s}_j\right)+\gamma {Z}_j+{d}_j+ \log \left({E}_{ijt}\right), $$

The rate ratio *r*
_*π*_ is a function of baseline treatment effect (*β*
_2_) and time-related treatment effect (*β*
_3_) : *r*
_*π*_ = exp(*β*
_2_ + 2*β*

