_3_). For each of the 1000 data sets, we estimated the same model and tested the hypothesis that *β*
_2_ + 2*β*
_3_ (the effect size in the third quarter) was significantly different from 0. The proportion of significant results represented the power of the study under the specific set of assumptions.

For the purposes of simulation, we assumed 63 sites in each stratum, for a total of 252 sites. Preliminary simulations indicated that larger general time trends (*β*
_1_) and larger number of patients in a physician panel both increased power. Based on this, our final simulations included very conservative assumptions of zero growth trend (*β*
_1_ = 0) and average eligibility size (*E*
_*jt*_) of 50 patients per physician at the practice. In the simulation, a general level of *E*
_*j*_ for site *j* was generated from a Poisson distribution of mean 50 × the number of physicians at the site. The value of *E*
_*jt*_ for a particular time period was calculated (and rounded to the nearest integer) as *E*
_*ij*_ + *e*
_*ijt*_, where *e*
_*ijt*_ ~ *N*(mean = 0, sd = 2). For each site *j* during period *t*, log(*C*
_*jt*_) was generated using equation (2). A value *C*
_*jt*_, the number of patients in compliance for site *j* during period *t* was generated from a Poisson distribution with mean *C*
_*jt*_.

Table 4 shows results after varying effect size parameters (*β*
_2_ & *β*
_3_), baseline compliance rate (*π*
_0_), site-level random effect variance (*σ*
_*d*_^2^), and patient eligibility levels (*E*). The current baseline compliance rates for the four measures are 49 % (blood pressure control), 33 % (LDL control for cholesterol), 35 %, (aspirin recommendation), and 20 % (smoking cessation referral). The number of patients that will be eligible in each 3-month period is based on an average physician roster of approximately 1,000 patients. Currently, 30 % of those patients have hypertension, 30 % have hyperlipidemia, and 20 % smoke. If we make a conservative estimate that 25 % of the patients will have an office visit per 3-month period, each eligible category will range from 50 to 75 patients. In Table 4, we use the lowest (most conservative) assumption of 50 patients, which reflects the likely size of the smoking group. At this level of eligible patients, we will have over 80 % power to detect a 2.2 % change, assuming a starting compliance rate of 20 % (increasing from 20.0 to 22.2 %) and between-site variance of 0.10 on the log scale.

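### The primary Poisson model does not match the variance of a proportion, so its standard errors are miscalibrated in a direction the protocol cannot show and the four tests do not run at the declared 0.05

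*Protocol article*

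**What the plan says.** Under Analysis plan, Aim 1, the primary outcomes are proportions of patients who reach clinical goals. Model (1) takes the number at goal in a site and quarter, C, with the log of the number eligible, E, as offset. For the distribution and random effects the text says "we will use a Poisson model with random site and provider within site effects". Equation (1) itself writes only a site intercept. Neither a site nor a provider intercept changes with time.

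On software: "The models will be fit using the LME4 package using R software". On error rate, each of the four hypotheses "will be tested separately with a two-sided test with *α* = 0.05".

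The Appendix (Power/effect size analysis) prefers a ratio to a difference "because of the specific Poisson distributions of the data and the model that we will be using". It draws the simulated counts from a Poisson distribution and analyses them with the same model. It gives the baseline rates as "49 % (blood pressure control), 33 % (LDL control for cholesterol), 35 %, (aspirin recommendation), and 20 % (smoking cessation referral". For panel size, "we use the lowest (most conservative) assumption of 50 patients, which reflects the likely size of the smoking group".

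**The concern.** C cannot exceed E. Given a site's rate p, C has binomial variance E·p·(1−p), while the Poisson family sets it to E·p. With p between 20 % and 49 % that difference is not negligible. A Poisson fit in lme4 has no free dispersion parameter to correct it.

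A second omission acts the other way. Model (1) has no term for a site's rate moving from quarter to quarter around its own level and the common trend. Any such movement adds variance that time-constant intercepts cannot absorb.

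At stake are the p-values and confidence intervals of all four primary tests. The two errors have different sizes for each outcome and each site size, so they cannot be expected to cancel. Depending on which dominates, the tests are conservative or give too many false positives.

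**Working it through.** **Inputs from the protocol article.** Baseline p = 0.20 (smoking), 0.33 (cholesterol), 0.35 (aspirin), 0.49 (blood pressure). Eligible patients per physician and quarter: 50 (1,000 × 20 % × 25 %) to 75 (1,000 × 30 % × 25 %). 252 simulated sites, four waves three months apart, between-site variance 0.10 on the log scale, two-sided α = 0.05. **Not given:** site-by-quarter variance τ². Physicians per site are not in the text at hand, so two are assumed where needed.

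**1. The plan's own power.** Generalised least squares information for the Poisson random-intercept model, with variance 1/(E·p) per site-quarter plus the site variance, Table 1 quarters including follow-up, and the Appendix contrast β2 + 2β3:

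| Case | Stated | Recomputed, 2 physicians per site |
|---|---|---|
| 20.0 to 22.2 %, E = 50 per physician | over 80 % | 85 % |
| Same effect, E = 70 | 92 % | 93 % |
| 2.7 points from 25 % | 91 % | 90 % |

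With 1, 1.5 or 3 physicians the first figure would be 62 %, 76 % or 95 %. The stated figures are thus plausible under a Poisson variance.

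**2. Poisson against binomial variance, τ² = 0.** SE ratio = √[E·p / (E·p·(1−p))] = 1/√(1−p). True size of the nominal 5 % test = 2·[1 − Φ(1.96 × ratio)].

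| Outcome | p | SE ratio | True size |
|---|---|---|---|
| Smoking | 0.20 | 1.12 | 2.8 % |
| Cholesterol | 0.33 | 1.22 | 1.7 % |
| Aspirin | 0.35 | 1.24 | 1.5 % |
| Blood pressure | 0.49 | 1.40 | 0.6 % |

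For the contrast β2 + 3β3 in the mixed model the analytic ratios are slightly smaller: 1.10, 1.21, 1.23 and 1.38.

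**3. Break-even with site-by-quarter variation.** On the log scale the model assumes 1/(E·p) per site-quarter, while the true variance is (1−p)/(E·p) + τ². They are equal when τ² = [1 − (1−p)]/(E·p) = 1/E, whatever p is. This is 0.020 at E = 50 and 0.0067 at E = 150 (75 patients × 2 physicians). As standard deviations these are √0.020 = 0.14 and √0.0067 = 0.08, or about 7 and 4 points around 49 %. As variances they are 20 % and 7 % of the 0.10 assumed between sites.

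**4. Simulation under no effect.** Binomial data, Table 1 control and intervention quarters, contrast β2 + 3β3, 800 runs per setting. Site effects were conditioned out as a stand-in for the random-intercept fit.

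| p | E | τ² | Model SE / true SD | Rejections at nominal 5 % |
|---|---|---|---|---|
| 0.49 | 50 | 0 | 1.39 | 0.6 % |
| 0.49 | 50 | 0.02 | 1.02 | 5.0 % |
| 0.49 | 50 | 0.04 | 0.83 | 9.5 % |
| 0.49 | 150 | 0 | 1.35 | 0.9 % |
| 0.49 | 150 | 0.01 | 0.93 | 6.5 % |
| 0.49 | 150 | 0.02 | 0.73 | 14.5 % |
| 0.49 | 150 | 0.04 | 0.52 | 32 % |
| 0.20 | 150 | 0.02 | 0.86 | 10.6 % |

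In separate runs with 290 sites and 1 to 3 physicians per site (assumed), a site-clustered robust SE held the rejection rate at about 3 to 7 % in every setting tried.

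**5. Effect on power, τ² = 0.** An effect with 80 % power under the Poisson variance lies 2.80 model SEs from zero. On binomial blood pressure data the Poisson test then has power Φ[(2.80 − 1.96) × 1.40] ≈ 88 %. A test with the correct variance has Φ[2.80 × 1.40 − 1.96] ≈ 97.5 %.

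**The case against.** Log-link Poisson regression is a recognised way to estimate a ratio of proportions, the Appendix gives its reason for working with a ratio, and variance estimation is often left to a statistical analysis plan, which is not shown here. That stands for the point estimates, which can be kept. It does not remove the point: the article itself fixes family, random effects, contrast, software and test level, and this combination does not deliver that level.

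A reader might infer more than the document supports:

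- *The standard errors are too wide and real effects will be missed.* This needs τ² = 0. The document gives no value, and its Discussion expects implementation fidelity to vary between practices. A random intervention effect alone (variance 0.01 to 0.02, E = 50) did not reverse the sign in the simulations, but modest site-by-quarter variation did.
- *The planned power is overstated.* It is not lowered by this choice, because the simulated counts already carry the Poisson variance. With purely binomial data the target would be exceeded (step 5).
- *About half the power for blood pressure is lost.* Simulations of a rise from 49.0 to 51.2 % gave 39 % power against 74 to 76 %, but that is a ratio of 51.2/49.0 = 1.045. The protocol's stated cases have ratios near 1.11. At 1.11, with the simulated SE of 0.0256 and true SD of 0.0177, the Poisson test has power Φ[(0.1044 − 0.0502)/0.0177], above 99 %.
- *The model implies impossible rates.* A log-normal site effect puts 1.2 % of sites above 100 % blood pressure control at variance 0.10, and 7.7 % at 0.25. No resulting bias in the primary contrast has been shown.

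Patients may also recur across quarters, since eligibility looks back 12 months. That effect was not quantified.

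**Conclusion.** The point holds as a calibration fault of unknown direction. The 12, 22, 24 and 40 % excess follows exactly from the stated baseline rates if sampling is purely binomial and site intercepts capture all other variation. Above τ² of roughly 1/E the same standard error is too narrow, and the simulated false-positive rate for blood pressure reaches 14.5 % at τ² = 0.02 and E = 150. Because E differs by outcome and by site, no single τ² calibrates all four tests. Any power loss is relative to a correctly calibrated analysis, not to the stated power. The simulated sizes rest on assumed physician numbers, on assumed values of τ², and on a conditional fit that stands in for the mixed model. The break-even at 1/E is an approximation for a single site-quarter.

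**What to change.** State one of two variance specifications for the Aim 1 tests and confidence intervals:

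- **Either** keep the log-link Poisson point estimates and use a site-clustered robust standard error. It works in both directions, is dependable with about 250 sites, and allows for patients recurring within a site.
- **Or** fit the same fixed effects as a binomial mixed model, `cbind(C, E-C)`, with a site-by-quarter random term, and report the month-12 effect as a standardised risk ratio and risk difference. A binomial model without that term is not a substitute, because it would be too narrow whenever such variation exists.

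Rerun the power simulation with binomial counts over a stated range of site-by-quarter variance, for example 0 to 0.04 on the log scale, as in the table above.

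The cost is a line of analysis wording, a rerun of the power program and, with the logit model, one standardisation step. The new power figure may be less favourable. Design and data collection do not change.

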## Background

In 2011, the US Department of Health and Human Services launched the Million Hearts Campaign with an explicit goal of preventing one million heart attacks and strokes by 2017 [1]. A core component of the campaign is to improve implementation and systematic delivery of ABCS treatment guidelines: (A) aspirin in high-risk individuals; (B) blood pressure control; (C) cholesterol management through guideline-recommended use of lipid lowering medications (i.e., statins); and (S) smoking cessation. In order to accelerate adoption of Million Hearts guidelines in primary care practices as well as build capacity for their ongoing implementation and dissemination, the Agency for Healthcare Research and Quality (AHRQ) launched EvidenceNOW—a national initiative that aims to transform health care delivery in small primary care practices by building critical infrastructure to integrate the most up-to-date research into practice to improve the heart health of their patients [2].

There is a strong rationale for targeting small practices (i.e., fewer than 10 providers). First, small practices continue to provide primary care for a significant proportion of the population. More than half of primary care office visits occur in small practice settings [3–5]. Second, small practices face daunting challenges in redesigning their system and care processes to meet regulatory requirements for practice transformation. Most small practices lack the resources and staff expertise related to information systems, goal setting, data analysis, and practice redesign to coordinate a complex set of multilevel system changes without external assistance [6]. One implementation strategy that may effectively overcome these barriers is practice facilitation (PF) [7, 8].

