Primary outcomes	• Aspirin: percent of patients aged 18 years and older with ischemic vascular disease (IVD) with documented use of aspirin or other antithrombotic. • Blood pressure management: 1) Percent of patients aged 18–85 who had a diagnosis of hypertension (HTN) and whose blood pressure (BP) was adequately controlled (<140/90). 2) Percent of patients aged 60–85 without diabetes (DM) or chronic kidney disease (CKD) with controlled BP (<150/90), 3) Percent aged 18–85 with DM or CKD with controlled BP (<140/90) • Cholesterol management: 1) Percentage of patients aged >21 diagnosed with ASCVD who are on statin therapy. 2) Percentage of patients aged >21 with history of LDL >190 mg/dL without ASCVD who are on statin therapy. 3) Percentage of patients aged 40–75 with diabetes without ASCVD and LDL 70–189 mg/dL who are on statin therapy • Smoking cessation support: Percentage of patients aged 18 years or older who were screened about tobacco use one or more times within 24 months and who received cessation counseling intervention if identified as a tobacco user.	EHR	Baseline, quarterly during intervention period, at the end of intervention (12 months), and 6 months post intervention
Secondary outcome: practice change capacity	• Organizational change process capacity • Adaptive reserve	Provider and staff survey	Baseline, at the end of intervention (12 months) and 6 months post intervention

The secondary outcome is changes in primary care practice capacity captured through the use of the change process capacity questionnaire and the 23-item adaptive reserve scale [31, 32]. These measures will be obtained through provider and staff surveys at three time points: baseline, immediately following the 12-month intervention and 6 months post-intervention.

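### The primary cholesterol outcome is statin therapy in Table 2, controlled cholesterol in model (1), and LDL control in the power Appendix, so the tested proportion is not fixed

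*Protocol article*

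**What the plan says.** The cholesterol outcome appears in four places in the Protocol article.

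- **Background:** the C of ABCS is "cholesterol management through guideline-recommended use of lipid lowering medications (i.e., statins"), a treatment measure.
- **Table 2 (Outcome measures and data source), primary outcomes:** three measures, all of them statin use. The first is "Percentage of patients aged >21 diagnosed with ASCVD who are on statin therapy". The second is "Percentage of patients aged >21 with history of LDL >190 mg/dL without ASCVD who are on statin therapy". The third covers patients aged 40–75 "with diabetes without ASCVD and LDL 70–189 mg/dL who are on statin therapy".
- **Analysis plan, Aim 1:** the outcome is first named as blood cholesterol management, but the definition of the count in model (1) runs, for outcomes (b) to (d), "b) had controlled blood pressure, (c) had controlled cholesterol, or (d) received smoking cessation counseling during period" t. The eligible pool is said to differ by outcome and to be described in Table 1. Table 1 holds only the stepped-wedge layout.
- **Appendix, Power/effect size analysis:** compliance is described as an appropriate cholesterol level. The baseline rates after blood pressure are listed as "33 % (LDL control for cholesterol), 35 %, (aspirin recommendation), and 20 % (smoking cessation referral"). The denominator is the 30 % of a physician's roster with hyperlipidemia.

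On the number of tests, Aim 1 says: "Each of the four hypotheses referring to the four primary outcomes will be tested separately with a two-sided test" at 0.05, without adjustment for multiplicity. Table 2 lists one aspirin, three blood pressure, three cholesterol and one smoking measure under primary outcomes.

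**The concern.** Being on a statin is a process measure taken from the medication record. Controlled cholesterol is a laboratory result. A patient with ASCVD who takes a statin but whose LDL is still high counts as a success under Table 2 and as a failure under model (1). A patient with well-controlled LDL and no statin does the reverse. These are not two names for one quantity.

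Practice facilitation could change prescribing without changing LDL within 12 months, so the cholesterol hypothesis could give different answers under the two definitions. A later report could cite this article for either.

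A related, smaller gap is that Aim 1 has one model each for blood pressure and cholesterol while Table 2 offers three measures for each. The article does not say which one is tested or whether they are pooled.

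**Working it through.** **1. The three versions side by side**

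| Place | Numerator | Denominator |
|---|---|---|
| Table 2 | On statin therapy | ASCVD, age >21; history of LDL >190 without ASCVD, age >21; diabetes without ASCVD, LDL 70–189, age 40–75 |
| Model (1) | Controlled cholesterol | Referred to Table 1, which has none |
| Appendix | Appropriate cholesterol level / LDL control (33 %) | Hyperlipidemia, 30 % of roster |

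The denominators differ in substance. A patient with hyperlipidemia but no ASCVD, no diabetes and no LDL above 190 is in the Appendix denominator and in none of the Table 2 groups. If the pointer is read as Table 2, model (1) puts a cholesterol-control numerator over statin-eligible denominators, which matches neither of the other two versions.

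**2. Mapping of measures to models**

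1 + 3 + 3 + 1 = 8 listed measures, against four models.

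The choice matters for blood pressure. A patient with hypertension aged 60–85 without diabetes or CKD, with systolic pressure from 140 to 149 and diastolic below 90, passes the second measure (<150/90) and fails the first (<140/90).

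For cholesterol, the first group is disjoint from the other two. The second and third can overlap, for example in a patient with diabetes whose LDL was once above 190 and is now 70–189. Pooling therefore needs a rule that counts each patient once.

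**3. The Appendix input and the stated power**

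The Appendix arithmetic gives 1,000 × 0.30 × 0.25 = 75 hyperlipidemia patients per physician per quarter, and 1,000 × 0.20 × 0.25 = 50 smokers. The remark that power is higher for cholesterol than for smoking rests on the 75, which is not a count of Table 2 statin-eligible patients.

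To check the stated power I used a large-sample approximation to the Appendix model:

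- four waves of 63 sites, β1 = 0, contrast β2 + 2β3;
- working covariance per site V = diag(1/μ_t) + σ²J, with J a matrix of ones, and information I = Σ 63·XᵀV⁻¹X summed over waves;
- SE = √(cᵀI⁻¹c) with c = (0, 0, 1, 2), and power = Φ(ln r / SE − 1.96).

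Physicians per site is not given in the visible text, so it is an assumption and is varied.

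- **Stated:** over 80 % for 20.0 to 22.2 % (r = 1.11), variance 0.10, 50 patients per physician. Recomputed: 60–63 % with 1 physician per site, 74–76 % with 1.5, 84–85 % with 2, 94–95 % with 3.
- **Companion figures at 2 physicians:** 93–94 % with 70 patients (stated 92 %), and 89–90 % for 2.7 points from 25 % (stated 91 %).

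The stated figures are plausible at about 2 physicians per site. They are not shown to be wrong.

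**4. What a change of measure could do**

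This is sensitivity only, with r = 1.11, variance 0.10, an assumed 2 physicians per site and follow-up quarters included.

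| Baseline rate | Eligible per physician | Power |
|---|---|---|
| 33 % | 75 | 99.5 % |
| 33 % | 50 | 96 % |
| 33 % | 25 | 79 % |
| 33 % | 10 | 50 % |
| 50 % | 50 | 99.5 % |
| 70 % | 50 | over 99 % |

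Smaller eligible groups lower power and a higher baseline rate raises it. The document gives neither value for statin use.

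**The case against.** The strongest reply is that the governing definition can be recovered. The Background and Table 2 agree on statins, Aim 1 opens with blood cholesterol management, the measures were set jointly across the seven EvidenceNOW groups, and the table pointer is evidently a misprint for Table 2. On that reading, controlled cholesterol is loose shorthand. This supports choosing statin therapy as the correction. It does not remove the contradiction, because the definition of the model's count is the text an analyst would program from.

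A second reply is that assigning Table 2 measures to models is commonly left to an analysis plan. The three cholesterol groups read naturally as one statin-eligible population, and the first blood pressure measure is the overall one. That is fair, and the mapping alone would not be a finding. It belongs in the same edit because the cholesterol count has to be rewritten anyway. For the same reason, a reader should not infer that the measure will be picked after the data are seen; the unseen plan may already name it.

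A reader might also infer that eight measures at 0.05 imply a 34 % chance of a false positive (1 − 0.95⁸ = 0.337). The document does not support this. It commits to four tests, and the measures overlap, so independence fails. For four independent tests the figure is 1 − 0.95⁴ = 0.185, which follows from the plan's openly stated choice not to adjust.

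Finally, no numerical power for cholesterol appears in the visible text, only the remark that it is higher than for smoking. The eligibility section also admits patients with hyperlipidemia, so that denominator is not wholly foreign. Both points stand.

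**Conclusion.** The point holds for the cholesterol outcome. One of the four primary hypotheses is defined as statin therapy in Table 2 and counted as controlled cholesterol in model (1). The power Appendix plans for LDL control in a hyperlipidemia population, and the cross-reference that should settle the denominator leads to the wrong table. This is wrong as printed, and an unseen analysis plan would not remove it.

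The conclusion rests on the text and needs no statistical assumption. It should not be read as showing that cholesterol power is overstated: the direction cannot be determined from this document, and the sensitivity figures depend on an assumed 2 physicians per site.

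The other wording differences are minor. Aspirin is documented use in Table 2 and a recommendation in the Appendix. Smoking is counseling in Table 2 and model (1) and referral in the Appendix. These affect planning inputs; model (1) itself stays close to Table 2 for both.

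**What to change.** 1. In Eq. (1), replace the controlled-cholesterol count with the number of patients on statin therapy, and take E_it from the Table 2 statin-eligible groups.
2. Correct the pointer for the eligible pools from Table 1 to Table 2.
3. State which blood pressure measure, and which cholesterol measure or pooled set, is tested in each of the four models, and report the others as secondary. One workable choice is the first-listed blood pressure measure and the three statin groups pooled with each patient counted once.
4. In the Appendix, replace the 33 % LDL-control rate and the 30 % hyperlipidemia share with the baseline statin rate and the size of the eligible groups. If these are not available, say that the statement of increased cholesterol power was derived for a different measure. Align the aspirin and smoking inputs with Table 2 in the same way.

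Items 1 to 3 are text changes and need no new data collection, since the Table 2 measures are already planned for extraction from the EHRs. Item 4 costs more: it needs a statin rate and group sizes that the article does not give, and a rerun of the simulation if a cholesterol power figure is wanted. The alternative sentence costs nothing. The changes should be dated before outcome data are analysed.
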